### Exploratory outcomes of the intervention study and follow-up

Leftover blood from clinical blood sampling will be studied regarding selected biomarkers and their relation to ROP development and intervention effect.

### Safety outcomes in the intervention study

Clinically significant changes (abnormalities) from the physical examination of the infant or abnormal laboratory values will be recorded as an AE, starting from the time of randomization until the intervention phase termination visit. Ongoing AE at the intervention phase termination visit will be followed until the event is resolved or stable. Especially signs of increased ocular pressure (> 20 mmHg) or abnormal growth (> 1 standard deviation difference in weight, length and head circumference) after the start of intervention will be monitored as these are well-recognized side effects of high-dose steroid treatment, although this treatment is considered to be low dose. Other collected study-specific AEs will be pulmonary haemorrhage, pneumothorax, bronchopulmonary dysplasia (BPD), pulmonary hypertension, hypotension, circulatory instability, surgical patent ductus arteriosus (PDA), medical PDA, hypoglycemia, hyperglycemia, insulin treatment (glucose > 10 mmol/L at 2 independent time points), necrotising enterocolitis (NEC), perforated gut, ileus, enterostomy, sepsis, meningitis, intraventricular haemorrhage (IVH), and hydrocephalus. For each AE the following data will be recorded: AE diagnosis, AE start and end date, action taken regarding AE, AE outcome (resolved, ongoing, death, or lost to follow-up) and AE causality (not related, possibly related, related). Any severe AE (SAE), death or life-threatening event will be reported from the investigator at each site to the PI within 24 h of knowledge of the event. The local investigator and PI can stop the intervention temporarily or discontinue the infant from the study. If the infant is discontinued from the study, proper study termination procedures, including examinations and samplings, must be followed accordingly. The PI must report discontinuation due to an AE/SAE immediately to Thea Nordic.

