**Data collection and study procedures**									
Informed consent	X								
Eligibility	X								
Medical history/characteristics of infant/mother	X								
ROP evaluations	X		X	X	X				
RetCam photography	X		X	X	X				
Randomization		X							
Dexamethasone/placebo intervention dispense/return		X	X	X	X	X	X		
ROP treatment with laser and/or anti-VEGF			X^c^	X^c^	X^c^				
Intraocular pressure	X^d^		X^d^	X^d^			X^d^		
MRI^e^ + Peapod						X^e^			
Physical examination		X				X		X	X
Weight, length, head circumference		X	X	X	X	X		X	X
Vital signs: SpO2, heart rate, blood pressure		X					X		
Blood samples		X^f^	X^f^	X^f^	X^f^	X^f^	X^f^		
Saliva cortisol		X	X	X	X		X	X	X
Urine sample		X				X	X		
Adverse events	X	X	X	X	X	X	X		
Visual outcome and refractive errors								X	X
Retinal morphology with OCT								X	X
Diagnoses and complications								X	X
Study termination		X	X	X	X	X	X	X	X

Study protocol version 4

Visit R0= Visit before start of intervention

Visit C1 = Clinical visit 1 (start of intervention)

Visit R1 = 1 week after start of intervention

Visit R2 = 2 weeks after start of intervention

Visit C2 = Clinical visit 2 (40 weeks PMA)

Visit T1 = 2 weeks after end of intervention

*Abbreviations*: *OCT* Coherence tomography, *PMA* Postmenstrual age, *ROP* Retinopathy of prematurity, *SpO2* Oxygen saturation, *VEGF* Vascular endothelial growth factor

^a^Visit RX = ROP Screening and intervention as many as required in order to be correctly followed-up regarding the monitoring and treatment of the ROP disease, procedures performed weekly

^b^Main study termination visit occurs two weeks after the last intervention or at earliest at 40 weeks PMA when maximum ROP should have occurred

^c^ROP treatment provided when required according to guidelines

^d^Intraocular pressure will be measured before intervention, 1 and 2 weeks after start of intervention and after end of intervention

^e^If performed in clinical routine, PeaPod in Gothenburg

^f^If clinical sample is taken left over blood is collected for analyses

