The following data on infant and mother characteristics and medical history will be collected:Infant’s birth characteristics: GA at birth, sex, birth weight (grams), birth length (cm), birth head circumference (cm), single/twin/triplet, age at inclusion in the study.Infant’s medical history: lung morbidities like BPD, circulatory instability and PDA, gut problems like ileus and NEC, infections like sepsis, IVH and hydrocephalus. All surgical interventions.Mother’s age (years) and mother’s medical history: pregnancy complications, preeclampsia, infection requiring antibiotics, diabetes, hypertension or other disease requiring medication, parity, in vitro fertilization.

Intraocular pressure will be measured, and samples for salivary cortisol will be taken before intervention and thereafter according to the study protocol. Vital signs such as oxygen saturation (SpO2), heart rate and blood pressure will be measured before and after the intervention. At all clinical study visits, weight, length, and head circumference will be recorded. Body composition with PeaPod at 40 weeks PMA will be performed at sites where PeaPod is available. Brain Magnetic Resonance Imaging (MRI) will be performed at 40 weeks PMA according to clinical routine. Glucose in urine will be monitored after the initial start of intervention and at 40 weeks PMA. If intervention continues after 40 weeks PMA, a urine sample will be taken two weeks after the completion of intervention at the study termination visit. Leftover blood from clinical sampling will be analyzed for biomarkers involved in ROP-related processes such as angiogenesis, neurogenesis and inflammation (Gothenburg site).

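### Table 2 schedules no physical examination or growth measurement at the termination visit that closes the adverse event window; separately, it starts adverse event recording before randomization

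*Protocol article*

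**What the plan says.** All references are to the protocol article.

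- **Safety outcomes in the intervention study**, on the source of AEs: "Clinically significant changes (abnormalities) from the physical examination of the infant or abnormal laboratory values will be recorded as an AE". The window is "starting from the time of randomization until the intervention phase termination visit". Two effects are singled out for monitoring: "signs of increased ocular pressure (> 20 mmHg) or abnormal growth (> 1 standard deviation difference in weight, length and head circumference". The section also lists specific diagnoses to be collected as AEs and records a start date for each event.
- **Study procedures and data collection at intervention phase visits**: "At all clinical study visits, weight, length, and head circumference will be recorded". The same section expects some infants to be on drops after 40 weeks PMA and adds a urine sample at termination for them.
- **Table 2, visit key and footnotes**: C2 is fixed at 40 weeks PMA. "Visit T1 = 2 weeks after end of intervention"; footnote b places T1 no earlier than 40 weeks PMA. RX visits are weekly and as many as ROP monitoring requires (footnote a).
- **Table 2, rows**: "Physical examination" and "Weight, length, head circumference" are both blank at T1. The AE row begins at R0, and randomization is marked only at C1.
- **Intervention**: drops are given for at most 12 weeks.

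**The concern.** The AE window closes at T1, yet one of the two named sources of AEs is not collected there. C2 is tied to postmenstrual age and T1 to the end of drops. The interval between them, in which no physical examination is scheduled, therefore lengthens as drops run further past 40 weeks. The infants with late or long exposure are the ones in whom a systemic steroid effect would most need to be looked for.

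Growth is treated differently from the other singled-out effect: intraocular pressure has a value at T1, and growth has no scheduled value at that visit.

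At the other end of the window, the text starts AEs at randomization and the table starts them one visit earlier. BPD, PDA, NEC, ileus, sepsis, IVH and hydrocephalus appear both among the study-specific AEs and in the medical history. A site following Table 2 could therefore enter a condition that predates randomization in either place.

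**Working it through.** No sample size, power or error-rate figure is involved. The check reads Table 2 by column and then follows the visit timeline.

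**Step 1. Table 2 by column**

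| Row | Visits marked | At T1? |
|---|---|---|
| Physical examination | C1, C2, 2 years, 5.5 years | No |
| Weight, length, head circumference | C1, R1, R2, RX, C2, 2 years, 5.5 years | No |
| Vital signs | C1, T1 | Yes |
| Intraocular pressure | R0, R1, R2, T1 | Yes |
| Saliva cortisol | C1, R1, R2, RX, T1, 2 years, 5.5 years | Yes |
| Urine | C1, C2, T1 | Yes |
| Adverse events | R0, C1, R1, R2, RX, C2, T1 | Yes |
| Randomization | C1 | – |

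Blood at T1 is only what is left over from a clinical sample (footnote f).

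**Step 2. Timeline**

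Let S be the PMA at the first drop and D the weeks of drops.

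- End of drops = S + D.
- T1 = the later of 40 and S + D + 2.
- Weeks of drops after the last physical examination = S + D − 40, if positive.
- Weeks from C2 to T1 = T1 − 40.

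D is at most 12. S is not given in the documents, so a range is assumed. With D = 12:

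| Assumed S | End of drops | T1 | Weeks of drops after C2 | Weeks from C2 to T1 |
|---|---|---|---|---|
| 32 | 44 | 46 | 4 | 6 |
| 34 | 46 | 48 | 6 | 8 |
| 36 | 48 | 50 | 8 | 10 |
| 38 | 50 | 52 | 10 | 12 |

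A full 12-week course outlasts C2 whenever S exceeds 40 − 12 = 28 weeks. A shorter course does so whenever S + D exceeds 40; for example, S = 36 and D = 8 gives 44 − 40 = 4 weeks. If drops end by 38 weeks PMA, T1 and C2 coincide, and C2 supplies both the physical examination and the growth values.

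**Step 3. Growth**

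Growth is marked at the weekly RX visits, so it is followed during the course, including after 40 weeks. What is not scheduled is a value at T1. When T1 falls after C2, the unscheduled stretch runs from the last RX visit to T1, roughly the two weeks after the last drop.

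**Step 4. Start of the AE window**

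The safety section starts at randomization. Table 2 puts randomization at C1 and the first AE mark at R0, which its key places before the intervention starts. The two statements disagree by one visit.

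**The case against.** The strongest reply is that safety is still well covered at the end of the course. T1 includes vital signs, intraocular pressure, saliva cortisol, urine and AE recording, and AEs are also recorded at every RX visit. Laboratory values are an equal source of AEs, and most of the listed diagnoses would be known from routine care. This stands. A reader might infer from the blank T1 cells that the longest-exposed infants have no end-of-course safety assessment, or no growth data late in the course. Table 2 does not support either inference.

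A reader might also see the text contradicting Table 2 on what T1 contains. That is not established. Table 2 heads only C1 and C2 as clinical visits, so the sentence on growth at clinical visits may not reach T1. The Discussion promises growth monitoring only during the intervention and at 40 weeks PMA. The final examinations required under Subject withdrawal and in the safety section concern withdrawn or discontinued infants, and are not said to be general physical examinations.

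On the R0 mark, a reader might infer that events before randomization will dilute the comparison between arms. Each AE has a recorded start date, so such events can be separated at analysis, and nothing says that R0 entries will be counted. The R0 mark is also unrelated to the missing examination.

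Finally, a journal article condenses the full protocol. But Table 2 is labelled with the protocol version and itemises the content of T1, so the blank cells are stated content, not detail left elsewhere.

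**Conclusion.** The point holds in a limited form. The AE window runs to T1, physical examination is a named source of AEs, and none is scheduled there. For infants still on drops after 40 weeks PMA, no physical examination is scheduled between C2 and 2 years. With 12-week courses and assumed starts at 32 to 38 weeks PMA, 4 to 10 weeks of drops follow the last examination, and T1 comes 6 to 12 weeks after it. These figures depend on the assumed starts and on the maximum duration. The documents do not show how many infants will be affected, and infants whose drops end by 38 weeks are not.

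For growth, the gap is confined to the period between the last RX visit and T1, but it removes the scheduled post-course value for one of the two effects singled out for monitoring. The AE mark at R0 is a separate and smaller inconsistency with the text. The primary analysis is unaffected. The change is worth making because the examination gap widens with late exposure and can be closed at an existing visit.

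**What to change.** 1. In Table 2, mark physical examination and weight, length and head circumference at T1, done once when T1 and C2 coincide.
2. Remove the AE mark at R0, so that the table agrees with the safety section. State that conditions with onset before randomization go to medical history, and that only new or worsened events from randomization to T1 count as AEs.

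The cost is an amendment to Table 2 and a few minutes at a visit that already takes vital signs, intraocular pressure, saliva and urine. No visit is added. The article reports recruitment as ongoing, so the change can still benefit infants who have not yet reached T1.

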### Study procedures and data collection at intervention phase visits

All data are collected and stored in agreement with good clinical practice guidelines and in accordance with the General Data Protection Regulation.

Table 2 presents the study schedule for visits and procedures in the “intervention phase” (main) study and the “extension” (follow-up) study. The intervention phase study termination visit is planned to occur approximately at PMA 40 weeks or two weeks after the eye drop intervention ends, regardless of regression of ROP or ROP treatment.

**Table 2 Tab2:** DROPROP study schedule for study procedures and data collection

	**Intervention phase (Main) study**							**Extension study**	
**Procedures**	**ROP screening**	**Clinical visit**	**ROP screening/intervention**			**Clinical visit (40w PMA)**	**Termination ****visit**^**b**^	**Follow-up**	
	**Visit R0**	**Visit C1**	**Visit R1**	**Visit R2**	**Visit RX**^**a**^	**Visit C2**	**Visit T1**	**2 yrs** **Visit F1**	**5.5 yrs Visit F2**
**Data collection and study procedures**									
Informed consent	X								
Eligibility	X								
Medical history/characteristics of infant/mother	X								
ROP evaluations	X		X	X	X				
RetCam photography	X		X	X	X				
Randomization		X							
Dexamethasone/placebo intervention dispense/return		X	X	X	X	X	X		
ROP treatment with laser and/or anti-VEGF			X^c^	X^c^	X^c^				
Intraocular pressure	X^d^		X^d^	X^d^			X^d^		
MRI^e^ + Peapod						X^e^			
Physical examination		X				X		X	X
Weight, length, head circumference		X	X	X	X	X		X	X
Vital signs: SpO2, heart rate, blood pressure		X					X		
Blood samples		X^f^	X^f^	X^f^	X^f^	X^f^	X^f^		
Saliva cortisol		X	X	X	X		X	X	X
Urine sample		X				X	X		
Adverse events	X	X	X	X	X	X	X		
Visual outcome and refractive errors								X	X
Retinal morphology with OCT								X	X
Diagnoses and complications								X	X
Study termination		X	X	X	X	X	X	X	X

Study protocol version 4

Visit R0= Visit before start of intervention

Visit C1 = Clinical visit 1 (start of intervention)

Visit R1 = 1 week after start of intervention

Visit R2 = 2 weeks after start of intervention

Visit C2 = Clinical visit 2 (40 weeks PMA)

Visit T1 = 2 weeks after end of intervention

*Abbreviations*: *OCT* Coherence tomography, *PMA* Postmenstrual age, *ROP* Retinopathy of prematurity, *SpO2* Oxygen saturation, *VEGF* Vascular endothelial growth factor

^a^Visit RX = ROP Screening and intervention as many as required in order to be correctly followed-up regarding the monitoring and treatment of the ROP disease, procedures performed weekly

^b^Main study termination visit occurs two weeks after the last intervention or at earliest at 40 weeks PMA when maximum ROP should have occurred

^c^ROP treatment provided when required according to guidelines

^d^Intraocular pressure will be measured before intervention, 1 and 2 weeks after start of intervention and after end of intervention

^e^If performed in clinical routine, PeaPod in Gothenburg

^f^If clinical sample is taken left over blood is collected for analyses

The following data on infant and mother characteristics and medical history will be collected:Infant’s birth characteristics: GA at birth, sex, birth weight (grams), birth length (cm), birth head circumference (cm), single/twin/triplet, age at inclusion in the study.Infant’s medical history: lung morbidities like BPD, circulatory instability and PDA, gut problems like ileus and NEC, infections like sepsis, IVH and hydrocephalus. All surgical interventions.Mother’s age (years) and mother’s medical history: pregnancy complications, preeclampsia, infection requiring antibiotics, diabetes, hypertension or other disease requiring medication, parity, in vitro fertilization.

Intraocular pressure will be measured, and samples for salivary cortisol will be taken before intervention and thereafter according to the study protocol. Vital signs such as oxygen saturation (SpO2), heart rate and blood pressure will be measured before and after the intervention. At all clinical study visits, weight, length, and head circumference will be recorded. Body composition with PeaPod at 40 weeks PMA will be performed at sites where PeaPod is available. Brain Magnetic Resonance Imaging (MRI) will be performed at 40 weeks PMA according to clinical routine. Glucose in urine will be monitored after the initial start of intervention and at 40 weeks PMA. If intervention continues after 40 weeks PMA, a urine sample will be taken two weeks after the completion of intervention at the study termination visit. Leftover blood from clinical sampling will be analyzed for biomarkers involved in ROP-related processes such as angiogenesis, neurogenesis and inflammation (Gothenburg site).

### Extension study

In an extension part of the study, an ophthalmological follow-up at 2 and 5.5 years of age will evaluate the child’s best-corrected vision with an age-appropriate visual chart, refractive errors in cycloplegia, ocular motility, strabismus, nystagmus, and stereopsis. Retinal morphology with ocular coherence tomography (OCT) will be performed to evaluate the optic disc and maculae region. Neonatal and ophthalmological diagnoses and complications, as well as children’s growth parameters, will be collected at follow-up.

### Sample size

Natural history studies of ROP suggests that 50% of infants with ROP stage 2 in posterior zone II with haemorrhage or ROP stage 3 in zone II develop Type 1 ROP needing treatment [1]. We aim to reduce the number of infants progressing to severe ROP needing treatment with laser and/or anti-VEGF by 60%. Assuming 50% of infants need ROP treatment in the placebo group and 20% in the dexamethasone group, alpha 0.05, using a two-sided Fisher’s exact test, would require 45 infants to be included per study group (1:1 ratio), in total, 90 infants excluding dropouts, to achieve a power of 80%. Taking into account a 10% drop-out rate, five infants per study group and thus 100 infants in total will need to be included.

### Data monitoring

The data will be entered into a database, where internal review and programmed computer checks will be used to identify selected protocol violations and data errors. A statement will be obtained from each infant’s parents/guardians participating in the trial permitting the release of the infant’s medical records as necessary for monitoring or inspection by authorized personnel for the PI and Regulatory Authorities.

#### Case report forms

The PI will be responsible for the database containing the information collected in the study retrieved from the eCase Report Forms (eCRFs). The eCRFs will be developed using the HOPE platform from ADDI Medical (www.addimedical.se).

#### Data monitoring committee

A Data Monitoring Committee (DMC) will be appointed, including an independent group of experts in the area that are not the Study PI or part of the study’s steering committee, with one ophthalmologist, one neonatologist, and one epidemiologist, that will scrutinize the data prepared by a non-voting statistical programmer. Two planned closed DMC meetings will be held, the first when 35% of the infants have been followed until the main study ends, and the second when 70% of the infants have been followed until the main study ends. DMC will analyse data for efficacy (benefit) and safety (harm) at both time points. Ó’Brian-Flemming group sequential boundaries on the positive side will be applied for evaluation of potentially halting the trial because benefit has been shown, and a z-value exceeding 2.40 will be applied for evaluation of potentially halting the trial because harm has been shown. DMC may decide, given the descriptive data to not perform formal statistical interim tests if there is no sign of need for formal analyses for stopping for harm and stopping for efficacy. The DMC will not be responsible for stopping the study for futility. Given that the formal statistical interim tests are performed, the final *p*-values must be updated based on the number of interim tests performed. DMC may also, if necessary, schedule additional DMC meetings between planned closed meetings.

Information about study results will be strictly held within the closed DMC group. After a closed DMC meeting, the PI and the study’s steering committee will only receive a recommendation to stop or continue the study.

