### Statistical analysis

All detailed statistical methods will be documented in a statistical analysis plan.

All analyses will be performed using either SAS software version 9.4 or later (SAS Institute Inc, Cary, NC, USA) or SPSS software version 26.0 or later (IBM Corp, Armonk, NY).

For tests between two groups, Fisher’s exact test will be used for dichotomous variables, Mantel–Haenszel Chi-square trend test for ordered categorical variables, Chi-square test for non-ordered categorical variables and Fisher’s nonparametric-permutation test for continuous variables. All efficacy evaluations will be adjusted for centre (strata in randomization) and gestational age (the most prominent risk factor). The difference between the two study arms with respect to binary outcomes such as the primary variable will be evaluated using logistic regression, for time-to-event data using Cox proportional hazards model, for number of recurrences per follow-up time using Poisson regression, for continuous outcomes using analysis of covariance (ANCOVA) or Fisher’s non-parametric permutation in case of not normally distributed data, and continuous outcomes repeatedly measured over time using mixed models for repeated measures.

All tests will be two-tailed. The primary analysis will be considered confirmed if *p* < 0.05.

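### The DMC may decide from the interim data whether a look becomes a formal test, and the final correction counts only tests performed, so the two-sided 5% level is not guaranteed

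*Protocol article*

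**What the plan says.** The Data monitoring committee section plans two closed meetings, when 35% and 70% of infants have completed the main study. Efficacy and harm are to be analysed at both. O'Brien-Fleming limits apply on the benefit side only, and a separate limit of z = 2.40 applies to harm. Three further provisions matter here:

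- **Testing is optional.** The "DMC may decide, given the descriptive data to not perform formal statistical interim tests if there is no sign of need for formal analyses". The option covers efficacy as well as harm.
- **The correction follows that option.** If interim tests are performed, the final p-values "must be updated based on the number of interim tests performed".
- **More meetings are possible.** "DMC may also, if necessary, schedule additional DMC meetings between planned closed meetings".

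The Statistical analysis section states "All tests will be two-tailed" and "The primary analysis will be considered confirmed if *p* < 0.05", without mentioning interim looks. The Sample size section uses a two-sided alpha of 0.05 with no allowance for interim testing.

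**The concern.** A stopping opportunity uses alpha because the trial could have been declared positive at that point. This is so whether or not a p-value is then computed. Under the stated rule, the data that decide whether to test are the same data that would be tested. They must be compared by arm if they are to show a need to stop for benefit or harm. Paths with a strong interim result can win early. Paths with a weak one are treated as if no look had taken place and keep the full 0.05 at the end. Alpha is available on every path but charged only on some.

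Two things are at stake. One is the error rate of the trial's single confirmatory claim. The other is whether its criterion is fixed in advance, since a committee that has seen interim results would in effect choose the final threshold.

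**Working it through.** **Inputs from the protocol article.** Looks at 35% and 70% (Data monitoring committee); two-sided alpha 0.05 (Sample size; Statistical analysis); "Assuming 50% of infants need ROP treatment in the placebo group and 20% in the dexamethasone group", 45 per group, two-sided Fisher's exact test, 80% power (Sample size).

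**Assumptions.** The information fraction equals the fraction of infants followed. The test statistic behaves as a normal process with correlation √(t₁/t₂) between looks. The article does not say which O'Brien-Fleming form is meant, so both are shown. A harm stop is not counted as confirming the primary analysis.

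**1. The plan's own figure.** Exact enumeration of Fisher's test at 50% versus 20% gives power 80.2% at 44 and 81.5% at 45 per group. The continuity-corrected formula gives 45. Then 45/(1 − 0.10) = 50 per group, 100 in total. The stated sample size reproduces.

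**2. Limits if both looks are charged (benefit side, one-sided 0.025).** The Lan-DeMets form spends α(t) = 2[1 − Φ(z₀.₀₁₂₅/√t)]. The classical form uses c/√t with c solved for total 0.025.

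| Form | z at 35% | z at 70% | z at end | Final nominal two-sided p |
|---|---|---|---|---|
| Lan-DeMets | 3.613 | 2.441 | 2.000 | 0.0455 |
| Classical | 3.397 | 2.402 | 2.010 | 0.0445 |

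With these limits the benefit-side error is 0.0250.

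**3. Worst case under the stated rule.** The DMC tests only when a limit would be crossed, and otherwise the final critical value stays at 1.960. The benefit-side error is 1 − P(Z₁ < b₁, Z₂ < b₂, Z₃ < 1.960):

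- Lan-DeMets: 0.0271, an excess of 0.0021; with 0.025 on the other side, 0.0521 in total.
- Classical: 0.0275, an excess of 0.0025; in total 0.0525.

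Simulation gives 5.19% and 5.23%, which agrees within simulation error.

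**4. Milder behaviour.** If the DMC tests whenever the interim Z exceeds a threshold and corrects for the tests run, the two-sided error (8 million simulated null trials) is:

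| Test if interim Z exceeds | Two-sided error |
|---|---|
| 0.5 | 4.99% |
| 1.0 | 5.01% to 5.02% |
| 1.5 | 5.07% to 5.09% |
| 1.96 | 5.14% to 5.18% |
| 2.3 | 5.18% to 5.23% |

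**5. Extra meetings.** If two further efficacy looks were held (assumed at 50% and 85%, Lan-DeMets), the worst case would be 0.0290 + 0.025 = 0.0540.

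**6. The number of tests does not determine the correction.** Under Lan-DeMets, one test at 35% gives a final z of 1.961, whereas one test at 70% gives 2.000. Timing matters as well as number.

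**7. Cost of charging both looks.** At 45 per group, Fisher power with only the final threshold lowered is 79.5% (0.0455 or 0.0445). Counting the chance of stopping early for benefit, it is about 80%. The loss from 81.5% is about 1.5 points.

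**The case against.** The strongest reply is that the safeguards are already substantial: conservative limits, two planned looks, an independent closed committee, and a compulsory correction whenever a test is run. Skipping is allowed only where nothing suggests a need to test, and a cautious DMC would test well below the boundary, with almost no inflation. This stands. It limits the claim to a level that is not guaranteed. A reader might infer that the 5% level is actually exceeded, but the article does not fix how readily the DMC tests.

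Other stronger readings also fail:

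- **A contradiction with the 0.05 criterion.** The article says the final p-values are updated, so 0.05 can be read as applying to the updated value. That is coherent, but the update still depends on the DMC's choice.
- **An error of 5.4% to 5.5%.** This requires O'Brien-Fleming limits on both sides. The plan has them on the benefit side only.
- **Unplanned efficacy testing.** The article permits extra meetings. It does not say efficacy is tested there, and any test that was run would enter the count.
- **An unrecorded decision.** Nothing says the DMC's choice would go undocumented.

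Fisher's test is also conservative: at 45 per group its true size is about 2.7% to 3.2% (common rates 0.50 and 0.35), which would absorb the excess. But the Statistical analysis section evaluates the primary variable by adjusted logistic regression, so that margin cannot be relied on.

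Numerical limits and the spending function may properly sit in the SAP, and their absence is not the point. The data-dependent rule is stated in the article itself, and an SAP that always charged alpha would contradict it.

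**Conclusion.** The concern holds as a gap in error control, small in size. For the two planned looks the worst-case excess is about 0.2 to 0.25 percentage points, on the benefit side and in the two-sided total alike. It falls to nothing if the DMC tests readily. These figures rest on information fractions of 0.35 and 0.70, the normal approximation and benefit-side limits of either O'Brien-Fleming form.

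The more practical consequence is ambiguity. A final nominal p between about 0.0455 (or 0.0445) and 0.05 would confirm the primary analysis if the interim tests had been skipped and fail if they had been performed. The point should be fixed. It is not serious enough to call the design unsound.

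**What to change.** - **Data monitoring committee section:** replace the count-of-tests correction with a rule that alpha is charged at both planned efficacy looks whether or not a formal test is computed. Use a pre-specified O'Brien-Fleming boundary or spending function at the actual information fraction. Either form will do.
- **Additional meetings:** restrict them to safety, or spend alpha there too.
- **Statistical analysis section:** state one criterion. Either compare the nominal p with the resulting final limit (about 0.0455 for Lan-DeMets or 0.0445 for classical at 35% and 70%), or compare an interim-adjusted p-value with 0.05. Doing both would correct twice.

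The cost is wording in the protocol and in any SAP or DMC charter, plus about 1.5 points of power. Power stays at essentially the planned 80% with 45 per group, so no sample-size change is needed. The article reports recruitment as ongoing. The change is best made before the DMC sees comparative efficacy data; if a look has already been held, it should be charged at its actual information fraction.
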